### Participant timeline

Pregnant females will be recruited at 14–16 weeks of gestation and receive intervention strategy at 32–36 weeks of gestation. Their infants will be followed-up for 2 years after birth. Clinical follow-up will be conducted in the hospital at 1, 3, 6, 8, and 12 months of age, and telephone follow-up will be conducted at 2, 4, 5, 10, and 24 months of age. Two specific pediatric attending doctors are responsible for the clinical follow-up of the infants. Infants suspected of having AD will be referred to the pediatric dermatology clinic, and two designated pediatric dermatologists will jointly diagnose and assess disease severity. Questionnaire surveys will be completed at each clinical and telephone follow-up. Parents will be instructed to contact the project team immediately and take the infant to two designated pediatric dermatologists for diagnosis and treatment if the baby is suspected of developing AD during 0–2 years of age. A detailed flowchart of the study is shown in Figure 1.

**Figure 1 fig1:**
[figure not shown]
Timeline of the study.

### Data collection and sample collection

Clinical follow-up of the infants will be conducted at 7 and 42 days of age, and telephone follow-up will be conducted at 6, 12, and 24 months of age. Questionnaire surveys will be completed at each clinical and telephone follow-up. The infant-specific questionnaire is designed based on the International Study on Asthma and Allergy in Children. Detailed information on birth parity, number of births (single or multiple births), gestational age, mode of delivery, weight (including birth weight), length (including birth length), feeding mode (breast, formula-, or mixed-fed), maternal and infant exposure to antibiotics and probiotics, parental smoking, family history of allergic diseases, infection, and other potential confounding factors will be recorded.

The mother’s feces will be collected within 1 week before intervention with solid beverage and the first week after delivery, whereas breast milk samples (approximately 5–10 mL each time) will be collected at 1–6 (colostrum), 7–15 (transitional milk), and 16–30 (mature milk) d after childbirth. Cord blood will be collected at the time of birth. Fecal samples (approximately 0.5–6 g each time) will be collected from infants in the colostrum, during transitional lactation, and at the ages of 1, 6, and 12 months after birth.

The maternal dietary survey is designed to be carried out before and after probiotic intervention (that is, 6 months after delivery). The dietary and nutritional status survey will be conducted using a 24-h dietary recall method to investigate the intake of various foods by the study participants within 3 days. Their energy and nutrient intake will be analyzed. The food frequency questionnaire will be used to collect information on the types and frequencies of food intake among all study participants and evaluate their dietary structure.

### Outcomes

#### Primary outcomes

In both stages of the trial, the cumulative incidence of AD within 2 years of delivery will be analyzed as the primary outcome. The diagnosis of AD is based on the Williams standard, as previously described, which is widely applicable to outpatient and general population epidemiological investigations in research (Williams et al., 1994). Skin itching is the primary criterion. The secondary criteria are as follows: (1) history of skin involvement on the flexor side, including the cubital fossa, cochineal fossa, anterior malleolus, and neck; (2) history of asthma, allergic rhinitis, or AD in first-degree relatives of children under 4 years of age; (3) history of dry skin throughout the body; (4) eczema on the flexed side (on the cheek or forehead and limbs on the extended side in children under 4 years of age); and (5) onset before the age of 2 years. Infants who meet the main criteria, along with three or more secondary criteria, will be diagnosed with AD. Once diagnosed with AD, disease severity will be assessed using the SCORAD index. Accordingly, infants will be divided into mild (SCORAD: 0–24 points), moderate (SCORAD: 25–50 points), and severe (SCORAD: >50 points) groups (Oranje et al., 2007).

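### The AD rule's lesion-history item names only flexor sites and the neck, while its eczema item is adapted to under-4s, so some infant cases fall one item short

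*Protocol article*

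**What the plan says.** Under Primary outcomes, the protocol article defines AD as one main criterion, "Skin itching is the primary criterion", plus a count: "Infants who meet the main criteria, along with three or more secondary criteria, will be diagnosed with AD". The five secondary items are:

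- Item 1: "1) history of skin involvement on the flexor side, including the cubital fossa, cochineal fossa, anterior malleolus, and neck"
- Item 2: "2) history of asthma, allergic rhinitis, or AD in first-degree relatives of children under 4 years of age"
- Item 3: "3) history of dry skin throughout the body"
- Item 4: "4) eczema on the flexed side (on the cheek or forehead and limbs on the extended side in children under 4 years of age"
- Item 5: "5) onset before the age of 2 years"

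The outcome is cumulative incidence within two years of delivery. Eligibility criteria admits families through asthma, eczema, food allergy or allergic rhinitis in a parent or earlier child. Participant timeline places hospital visits at 1, 3, 6, 8 and 12 months, and "telephone follow-up will be conducted at 2, 4, 5, 10, and 24 months of age". Suspected cases go to two designated dermatologists, and parents are told to make contact at once if they suspect AD.

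**The concern.** No child in the trial is older than 2 when the outcome is determined. Item 4 allows for that by naming the infant sites. Item 1 does not, yet it is the only item worded as a history of lesions. With a cumulative outcome, an episode that resolved before the child was examined would naturally be credited through item 1, and that credit is available only if the lesions were at flexor sites or the neck. Two infants with the same course of disease could then be classified differently because of body site, and the one who loses is the one with lesions where the rule itself expects them at this age. At stake is the classification of some primary-outcome events in both stages.

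**Working it through.** **Enumeration of the rule.** The article states no figure to reproduce here, so I scored the rule directly. Take an itchy infant with lesions only at cheek, forehead or extensor sites. Item 1 is then 0 as written, and item 5 is 1 for any onset within follow-up. Items 2, 3 and 4 vary. The last column credits item 1 for the infant sites.

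| Item 2 (family) | Item 3 (dry skin) | Item 4 (eczema) | As written | Item 1 age-matched |
|---|---|---|---|---|
| 1 | 1 | 1 | 4, AD | 5, AD |
| 1 | 1 | 0 | 3, AD | 4, AD |
| 1 | 0 | 1 | 3, AD | 4, AD |
| 1 | 0 | 0 | 2, not AD | 3, AD |
| 0 | 1 | 1 | 3, AD | 4, AD |
| 0 | 1 | 0 | 2, not AD | 3, AD |
| 0 | 0 | 1 | 2, not AD | 3, AD |
| 0 | 0 | 0 | 1, not AD | 2, not AD |

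Three of the eight profiles change:

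- **Row 4:** atopic family, no dry skin, eczema cleared by assessment (items 2 and 5 only).
- **Row 7:** family eligible through food allergy alone, which item 2 does not list; no dry skin, active eczema (items 4 and 5 only).
- **Row 6:** the same kind of family, with dry skin but cleared eczema (items 3 and 5 only).

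Row 3, the typical enrolled case without dry skin, is AD either way.

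**How large could the loss be?** The documents give none of the shares needed, so all four below are assumptions, treated as independent: f = true cases at infant sites only; d = with general dry skin; c = cleared before assessment; a = food-allergy-only families.

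Missed as written = f × [(1−a)·c·(1−d) + a·((1−c)(1−d) + c)] + (1−f)·a·c·(1−d)

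Missed with item 1 age-matched = a·c·(1−d)

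- **Low** (f 30%, d 80%, c 5%, a 5%): 0.3 × (0.0095 + 0.0120) + 0.7 × 0.0005 = 0.7%; age-matched 0.05%.
- **Middle** (60%, 50%, 20%, 10%): 0.6 × (0.09 + 0.06) + 0.4 × 0.01 = 9.4%; age-matched 1.0%.
- **High** (80%, 30%, 40%, 20%): 0.8 × (0.224 + 0.164) + 0.2 × 0.056 = 32%; age-matched 5.6%.

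**Dependence on the reading of item 4.** If documented past eczema satisfies item 4, no case loses that item by clearing. Setting c = 0 leaves f·a·(1−d): 0.3 × 0.05 × 0.2 = 0.3%, 0.6 × 0.1 × 0.5 = 3.0%, and 0.8 × 0.2 × 0.7 = 11.2%. Only the food-allergy subset remains.

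**The case against.** A reader might infer that typical infant AD is scored as not AD. The documents do not support that. Item 1 is one of five optional items, item 5 is met by every case arising in follow-up, and item 2 is met by most families because of how they are recruited. The typical case therefore qualifies without item 1.

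The cleared-lesion subset rests on reading item 4 as current eczema. The article does not say so. Items 1 to 3 speak of a history and item 4 does not, which makes the reading natural but not certain. The visits in Participant timeline and the instruction to parents also limit how many cases clear unseen. They do not remove the problem: that schedule has no planned examination after 12 months.

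The food-allergy subset is partly a mismatch between Eligibility criteria and item 2, not a fault of item 1 alone. It also requires no dry skin, or eczema that has cleared.

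A reader might further infer that incidence is biased low and power is lost. With the middle shares and equal losses in both groups, 40% against 20% becomes 36.2% against 18.1%, and power at 74 per group (two-sided 5%, normal approximation) goes from 76% to 70%. But the calculation contains only true cases, so it can show only lost sensitivity. Items 2 and 5 are nearly automatic here, so the rule is largely itching plus one further item, which points towards leniency. An assumed 5% false-positive rate among non-cases alone gives 43% against 24% and power of about 69%. The net direction is not established.

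Finally, the article paraphrases a cited standard that cannot be checked here, and the operative scoring form may be fuller. That is a reason to verify the wording. As printed, the two items still disagree.

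**Conclusion.** The point holds in limited form. Items 1 and 4 use inconsistent sites for a cohort aged 0 to 2. Followed as written, the rule leaves some itchy infants one item short: those without dry skin whose infant-site eczema had cleared (conditional on item 4 meaning current eczema), and some from food-allergy-only families. The assumption-based range is about 0.7% to 32% of true cases; its width reflects the lack of any shares in the documents. No bias in incidence and no loss of power should be asserted. The inconsistency should be corrected because it sits in the primary-outcome rule, not because its effect is known to be large.

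**What to change.** Before unblinding:

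1. Reconcile items 1 and 4 so that item 1 carries the same under-4 sites as item 4, after checking both against the cited diagnostic standard. The site names in item 1 can be proofread at the same time.
2. State whether item 4 means eczema present at assessment or also documented earlier eczema.
3. Have the designated dermatologists record each of the five items separately.
4. Report incidence under the flexor-only wording as a sensitivity analysis.

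Item 2 need not change for this purpose: with item 1 age-matched, active infant-site eczema in a food-allergy-only family reaches three items.

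The cost is a clause or two in the outcome definition and item-level fields on the form, with no added visits or participants. The downside is some loss of specificity: with items 2 and 5 nearly automatic, a parent-reported past facial rash in an itchy infant could be enough to reach three items. Joint scoring by the dermatologists and the sensitivity analysis limit that risk and make it visible.

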## Methods

### Eligibility criteria

According to the World Allergy Organization guidelines, a child may be considered at high risk for allergy if a biological parent or sibling has a history of allergic rhinitis, asthma, eczema, or food allergy (Fiocchi et al., 2015). The recruited pregnant females with babies at high risk for AD must meet the following inclusion criteria: healthy pregnant female (14–16 weeks of gestation), the mother or father of the fetus, or previous child of the couple diagnosed with any of the allergic diseases, including asthma, eczema, food allergy, or allergic rhinitis. This information will be confirmed by specific recruiters prior to recruitment. The risk of developing AD in infants without a family history of allergies is approximately 27%, whereas that in infants with one or two parents with an atopic history increases to 37.9 and 50.0%, respectively (Böhme et al., 2003). The population we aim to recruit meets the recommended probiotic target audience according to the guidelines of the World Allergy Organization (Fiocchi et al., 2015). The exclusion criteria are as follows: pregnant female under 16 years of age, multiple pregnancies, known fetal abnormalities, oral administration of immunosuppressive drugs or antibiotics, heart valve disease or immunodeficiency, undergoing dental surgery under antibiotic prevention, history of transplantation or HIV, long-term continuous use or ongoing use or intent to use probiotics before admission, external fertilization pregnancy, previous participation in research, deemed unsuitable for inclusion in the study owing to other medical reasons, and gestational diabetes.

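### In this cohort two of the five secondary criteria for atopic dermatitis are met by design, so the rule of three or more works as itch plus one further item for most infants

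*Protocol article*

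**What the plan says.** The primary outcome in both stages is defined under Primary outcomes in the protocol article: "the cumulative incidence of AD within 2 years of delivery will be analyzed as the primary outcome". "Skin itching is the primary criterion", and it is mandatory. The counting rule follows: "Infants who meet the main criteria, along with three or more secondary criteria, will be diagnosed with AD".

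The five secondary criteria are (1) flexural involvement in the history, (2) "history of asthma, allergic rhinitis, or AD in first-degree relatives of children under 4 years of age", (3) a history of generalised dry skin, (4) visible eczema, with a site variant for children under 4, and (5) "onset before the age of 2 years".

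Eligibility criteria admits only families with an allergic history, through the mother, the father or a "previous child of the couple diagnosed with any of the allergic diseases, including asthma, eczema, food allergy, or allergic rhinitis".

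Participant timeline refers infants with suspected disease to dermatology, where "two designated pediatric dermatologists will jointly diagnose and assess disease severity". No section changes the list or the threshold for this population.

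**The concern.** A count of criteria separates cases from non-cases only through items that can differ between infants. The article supports the standard by its use in outpatient and general-population surveys, where family history and early onset vary. Here entry is restricted to allergic families and observation to the first 2 years, so one item is constant among possible cases and another nearly so. The threshold still reads as three of five, but two of the three are usually supplied by the design.

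What is at stake is the specificity of the sole primary endpoint. In the randomised stage, false positives at the same rate in every arm raise all incidences and shrink the contrast. In stage 2, which has no placebo arm, they would be added directly to the reported incidence. Severity grading is no backstop, because the mild SCORAD band starts at 0.

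**Working it through.** **1. Which criteria are fixed by design**

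| Secondary criterion | Status in this cohort |
|---|---|
| 1 Flexural history | can vary |
| 2 First-degree family history | met at entry, unless food allergy is the only family condition |
| 3 Generalised dry skin | can vary |
| 4 Visible eczema | can vary |
| 5 Onset before 2 years | met by every infant who can be a case |

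Mother, father and an earlier child of the same couple are all first-degree relatives. Of the four qualifying conditions, only food allergy is absent from criterion 2. This reads eczema in the entry criteria as atopic dermatitis in criterion 2.

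**2. Effective threshold**

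- Most families: 3 − 2 = 1 of criteria 1, 3 and 4, plus itch. Of the 2³ = 8 patterns of these three items, 7 qualify.
- Food-allergy-only families: 3 − 1 = 2 of criteria 1 to 4. While criterion 2 stays unmet, this means two of criteria 1, 3 and 4.

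**3. Illustration of the effect on the count**

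Assume that an itchy infant without the disease meets each varying item independently with probability q. The documents give no value for q.

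| q | ≥3 of 5, none automatic | ≥1 of 3, rule as it works here: 1 − (1 − q)³ | ≥2 of 3, criterion 5 left out: 3q²(1 − q) + q³ |
|---|---|---|---|
| 0.1 | 0.9% | 27.1% | 2.8% |
| 0.2 | 5.8% | 48.8% | 10.4% |
| 0.3 | 16.3% | 65.7% | 21.6% |

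These apply to itchy infants who are assessed, not to all infants without the disease, so they are not specificities for the trial.

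**4. Illustration of the effect on power**

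Inputs: 40% and 20%, and 74 per group before dropout (Sample size calculation); two-sided 5% (Statistical methods). The plan's 74 does not reproduce at its stated 2.5% error and 80% power: the pooled formula gives 82 per group one-sided. That is a separate matter, but it is why the baseline below is 76% and not 80%.

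Observed incidence = p × Se + (1 − p) × (1 − Sp).

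Power = Φ{[d − 1.96 √(2p̄(1 − p̄)/n)] / √[(p₁(1 − p₁) + p₂(1 − p₂))/n]}, where d is the difference and p̄ the mean of the two rates.

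- Baseline: d = 0.20, p̄ = 0.30, so (0.20 − 1.96 × 0.0753)/0.0735 = 0.71 and power is 76%.
- Specificity 90%: 0.40 + 0.60 × 0.10 = 0.46 and 0.20 + 0.80 × 0.10 = 0.28, so (0.18 − 1.96 × 0.0794)/0.0780 = 0.31 and power is 62%.

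| Sensitivity | Specificity | Observed rates | Relative risk | Power |
|---|---|---|---|---|
| 100% | 100% | 40% vs 20% | 0.50 | 76% |
| 100% | 95% | 43% vs 24% | 0.56 | 69% |
| 100% | 90% | 46% vs 28% | 0.61 | 62% |
| 100% | 80% | 52% vs 36% | 0.69 | 50% |
| 90% | 100% | 36% vs 18% | 0.50 | 70% |
| 80% | 100% | 32% vs 16% | 0.50 | 63% |

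The last two rows show what a stricter rule could cost if it misses true cases.

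**5. Stage 2**

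With no comparator, a true incidence of 20% would be reported as 24%, 28% or 36% at specificity 95%, 90% or 80%.

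**The case against.** The counting is hard to dispute; its consequence is open to argument.

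- **Specificity is assumed.** No section gives the rule's performance in this population. At 80%, 0.60 × 0.20 = 12% of placebo infants and 0.80 × 0.20 = 16% of active infants would be wrongly labelled. A reader might infer from the power table that the trial loses a third of its power. The documents do not support that. This objection stands.
- **Diagnosis is a pathway.** A false positive needs suspicion of disease, itch, one further item and the agreement of two dermatologists. This may well limit the error. But the article says that infants who meet the count are diagnosed, and no rule lets judgement override it. The objection stands in part.
- **The 40% may already contain misclassification.** It rests on reported incidences from other studies, measured with definitions not shown. Adding false positives on top may count some of them twice. This stands.
- **A stricter count can miss cases.** The flexural item has no infant variant, so an infant with itchy cheek eczema and neither flexural history nor generalised dryness would cease to be a case. At sensitivity 80% the power is 63%, about what specificity 90% costs. This stands, and it is why the stricter count need not be the primary one.
- **The standard is an established one.** The point does not dispute it; it concerns counting near-constant items in a selected sample.

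A reader might also infer that the definition favours one arm. Stage 1 is double-blind, so the expected error is the same in all arms: it attenuates the effect and costs power, but does not inflate the type I error.

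**Conclusion.** The point holds as a matter of counting. Criterion 5 cannot discriminate, and criterion 2 does so only for food-allergy-only families, so for the other infants the stated rule works as itch plus one of three items. That rests on Eligibility criteria and Primary outcomes alone, with eczema read as atopic dermatitis.

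That specificity is lower as a result is plausible but not shown. The power figures of 69%, 62% and 50% against 76% are conditional on assumed specificities, full sensitivity and 40% versus 20% being true rates. It would go too far to say that the primary endpoint is unusable, or that the stage 1 result must be biased to the null by a known amount. Stage 2 is more exposed, because nothing there offsets an inflated incidence.

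Severity: should be fixed, because the rule defines the only primary endpoint of both stages and the remedy is cheap. It is not a condition for the trial to proceed.

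**What to change.** Before stage 1 is unblinded:

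1. Record itch and each of the five secondary criteria separately for every suspected case.
2. Define a count in which criterion 5 does not contribute: itch plus three of criteria 1 to 4. Where family history is present, this means two of flexural history, dry skin and visible eczema (4 of the 8 patterns instead of 7).
3. Pre-specify this count and the count as now written, one as primary and the other as a sensitivity analysis, and report both in each stage.

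This concerns how the trial endpoint is counted, not how infants are diagnosed or treated in the clinic.

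**Cost.** A few data fields, one paragraph of endpoint wording and one extra analysis. For infants already assessed, the items may have to be recovered from clinic notes, still blinded.

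**Downside.** The stricter count may miss true cases (63% power at sensitivity 80% with specificity 100%, relative risk still 0.50). Food-allergy-only families would need all three of criteria 1, 3 and 4, equally across randomised arms. Results would be less comparable with studies that use the criteria as stated. Reporting both counts lets a reader see how far the conclusion depends on the choice.

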#### Secondary outcomes

The severity of gastrointestinal and respiratory symptoms will be analyzed as a secondary outcome. Meanwhile, regulatory T cells in umbilical cord blood at birth (*n* = 20 for each group) will be analyzed via flow cytometry and the levels of transforming growth factor-β, interleukin (IL)-10, IL-12, IL-13, IL-4, interferon-γ (IFN-γ), tumor necrosis factor-α, and total IgE will be determined using enzyme-linked immunosorbent assay. Further, colostrum and 42-day mature milk level of transforming growth factor-β and IL-10 will be tested. Moreover, the relative abundance of sIgA-coated *L. reuteri* FN041 will be analyzed in breast milk and infant feces using strain-specific PCR, depending on the genome sequence information. *Lactobacillus* strains will be isolated and determined using 16 s rRNA sequencing, metagenomic sequencing will be performed to analyze *L. reuteri* FN041 (*n* = 10 for each group), and StrainPhlAn3 will be used to analyze the data at the strain level (Walsh et al., 2017).

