### Sample size calculation

The cumulative incidence of AD in high-risk infants at 1 and 2 years of age is reported to be approximately 40.1 and 41%, respectively, based on previous studies conducted in other countries (Rautava et al., 2012; Chaoimh et al., 2023). According to a previous study carried out in 2022 in our hospital, the overall point prevalence of AD in infants aged 0–24 months was 50.5% in Wuxi (Ding Y. et al., 2022). The expected cumulative incidence of AD after *L. reuteri* administration is approximately 20%, with a relative 20% reduction in AD incidence of 40% through intervention. Assuming that the first type of error would be 2.5% and the efficacy would be 80%, we calculated the sample using online tools.^1^ The sample size in each group would be 74. Considering a 10% dropout rate, each group should recruit 85 research subjects in the first stage. In the second stage of the trial, the sample size is expected to be approximately 500, which is considered sufficient to further verify the efficacy of maternal use of *L. reuteri* FN041 in the prevention of infantile AD.

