### Statistical methods

The data obtained in this study can be divided into continuous and categorical variables, which are presented as the mean ± standard deviation or median with interquartile range and frequency with percentage, respectively. Continuous variables will be analyzed for differences among the groups using ANOVA, whereas categorical variables will be analyzed using the chi-squared test. A two-sided *p-*value of <0.05 will be considered statistically significant.

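### If symptom severity is recorded in ordered grades, the stated chi-squared rule ignores their order and usually costs power on this secondary outcome

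*Protocol article*

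**What the plan says.** Protocol article, Outcomes, Secondary outcomes: "The severity of gastrointestinal and respiratory symptoms will be analyzed as a secondary outcome". The section gives no instrument, number of grades or time point for these symptoms.

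Protocol article, Statistical methods: "The data obtained in this study can be divided into continuous and categorical variables". The tests follow from that split: "Continuous variables will be analyzed for differences among the groups using ANOVA, whereas categorical variables will be analyzed using the chi-squared test". The significance level is two-sided 5%. Categorical data are to be shown as counts with percentages. No ordinal class of variable and no rank, trend or ordinal-model analysis is mentioned.

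Protocol article, Sample size calculation: "The sample size in each group would be 74". That number is for the incidence of atopic dermatitis. No sample size or power is stated for symptom severity.

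**The concern.** Severity has an order by its meaning. Pearson's chi-squared statistic does not change if the labels mild and severe are swapped, so it cannot use that order. On a four-grade scale it spreads a consistent shift over 3 degrees of freedom for one dose against placebo, and over 9 across the four groups, where an order-using comparison of two arms needs 1.

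At stake is the chance of detecting a real change in symptoms, for better or worse, on one named secondary outcome. The reader would also get no single estimate of how far the grades moved. The primary outcome, cumulative incidence of atopic dermatitis, is binary and is not affected.

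**Working it through.** **Inputs from the document.** 74 evaluable per group, two-sided 5%, four equal arms, chi-squared for categorical data.

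**Inputs assumed.** Number of grades, placebo distributions, and a proportional-odds shift with odds ratio (OR) 0.4 to 0.6 towards milder symptoms. The document gives none of these.

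**The plan's own figure.** There is none for this outcome. The 74 is the article's figure for 40% against 20% incidence at 80% power. The usual pooled formula at one-sided 2.5% gives [1.96√(2 × 0.3 × 0.7) + 0.842√(0.4 × 0.6 + 0.2 × 0.8)]² / 0.2² = 81.2, so 82; the 74 is not reproduced. That concerns the primary outcome and does not decide this point. I use 74 as the stated number and repeat the check at the 85 to be recruited.

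**One case by hand.** Placebo grades none/mild/moderate/severe 50/30/15/5%, OR 0.5. Halving the odds of being at or above each cut:
- at least mild: odds 1 → 0.5, probability 0.333
- at least moderate: odds 0.25 → 0.125, probability 0.111
- severe: odds 0.0526 → 0.0263, probability 0.026

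The dose arm is therefore 66.7/22.2/8.5/2.6%. The chi-squared noncentrality is n Σ(p − q)²/(p + q) = 74 × (0.0238 + 0.0116 + 0.0177 + 0.0078) = 4.51.
- On 3 degrees of freedom, 4.51 gives 40% power.
- Carried on 1 degree of freedom, the same 4.51 gives Φ(√4.51 − 1.96) = Φ(0.16) = 56%.

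The gap is the price of the two extra degrees of freedom.

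**Simulation.** 40,000 trials per row, one dose against placebo, 74 per arm; Pearson chi-squared against tie-corrected Wilcoxon. Differences are taken before rounding.

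| Placebo grades (%) | OR | Chi-squared power (%) | Wilcoxon power (%) | Loss (points) |
|---|---|---|---|---|
| 50/30/15/5 | 0.4 | 62.6 | 79.4 | 16.8 |
| 50/30/15/5 | 0.5 | 38.9 | 56.5 | 17.6 |
| 50/30/15/5 | 0.6 | 22.6 | 35.6 | 13.0 |
| 30/40/20/10 | 0.4 | 70.1 | 84.6 | 14.6 |
| 30/40/20/10 | 0.5 | 44.6 | 62.2 | 17.6 |
| 30/40/20/10 | 0.6 | 25.5 | 38.7 | 13.2 |
| 70/18/9/3 | 0.4 | 43.5 | 62.7 | 19.2 |
| 70/18/9/3 | 0.5 | 27.0 | 42.6 | 15.6 |
| 70/18/9/3 | 0.6 | 16.2 | 26.4 | 10.2 |
| 50/30/20 | 0.4 | 69.5 | 79.0 | 9.5 |
| 50/30/20 | 0.5 | 46.4 | 56.8 | 10.5 |
| 50/30/20 | 0.6 | 28.0 | 35.9 | 7.9 |
| 70/20/10 | 0.4 | 51.5 | 62.7 | 11.2 |
| 70/20/10 | 0.5 | 33.3 | 42.7 | 9.4 |
| 70/20/10 | 0.6 | 20.6 | 26.9 | 6.3 |

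**Sensitivity.**
- No effect: chi-squared rejects in 4.3 to 5.2% of trials and Wilcoxon in 4.8 to 5.2%. Both hold their level.
- Shift towards worse symptoms (OR 1.67 to 2.5), same distributions: loss about 8 to 17 points.
- 85 per arm, OR 0.4 to 0.6: loss about 7 to 19 points.
- Yes/no item (60/40%): the two tests agree within 1 point.
- Grades moving both ways, placebo 50/30/15/5% against dose 55/15/15/15%: chi-squared 64%, Wilcoxon 6%. Here the order-using test is far worse.

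**The case against.** The strongest reply is that the document never says severity is graded. A numeric symptom score would go to ANOVA, which does use order, and a present/absent item would lose nothing. A three-sentence statistical section in a journal article is a summary, and the scale and exact test for a secondary outcome are commonly left to a fuller document. This stands as far as it goes: the point must be conditional on three or more grades, and the absence of the scale is not itself the finding. It does not remove the point, because the section is not silent. It sorts all data into two classes and gives each a test, and a graded outcome falls under chi-squared.

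A reader might infer more than the text supports:
- **That the plan loses a fixed amount of power.** It does not follow; every figure above depends on assumed grades and effects.
- **That the mild, moderate and severe groups under Primary outcomes supply the scale.** Those are SCORAD classes for atopic dermatitis, not for these symptoms.
- **That other methods are excluded.** The section names two tests but does not forbid others.
- **That a significant result would have no readable direction.** The percentages by group would show it, and a four-group Kruskal-Wallis test gives no direction either. What is missing is a single estimate with an interval.
- **That safety monitoring depends on this test.** The Trial design section has adverse reactions recorded separately.

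**Conclusion.** The point holds in conditional form. If severity of gastrointestinal and respiratory symptoms is recorded in three or more ordered grades, the stated rule assigns it a valid but less efficient test. With three or four grades, a proportional-odds shift of OR 0.4 to 0.6 and 74 per arm, the loss is roughly 6 to 19 points of power. It is about nil for a yes/no item, and the sign can reverse when the effect is not a consistent shift. It concerns efficiency and reporting on one secondary outcome for which no power is claimed, and does not threaten the trial's validity.

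**What to change.** In Statistical methods, keep chi-squared for binary and unordered variables. Add one sentence: symptom severity recorded in ordered grades will be analysed with a proportional-odds model for each dose against placebo, reported as a common odds ratio with 95% confidence interval. A Wilcoxon test may be added in support, but it does not yield that odds ratio. Stating the symptom scale in the same place would settle whether the sentence applies.

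The change costs one sentence and needs no new data and no change to conduct. The downsides are that the proportional-odds assumption has to be checked and that power is lost against effects moving grades in both directions. The grade-by-arm table should therefore still be shown.
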